## Abstract

**Background:**

The aging population presents both opportunities and challenges. Both global and Malaysian statistics have shown that an increase in longevity is also marked by an increase in the time spent in poor health. A key measure of healthy aging is the ability to lead an independent life. This has implications not only for the individual’s quality of life but also for society as a whole; loss of independence with age is associated with increased economic burden and reduced workforce productivity. Understanding and subsequently addressing these age-related declines (slowing or reversing them) is critical in improving the health and societal challenges faced by older adults. However, most studies are focused on Western populations. The scarcity of interventions tailored to multiethnic Asian populations is compounded by the fact that existing measurements rely heavily on Western-designed psychometric instruments, which frequently fail in capturing true cognitive health because of large cultural and educational gaps.

**Objective:**

We aim to examine whether our long-term intervention packages can, over 4 years, significantly slow down the normal rate of aging-related decline in cognitive function and brain structure and function, as well as assess changes in aging-related salivary biomarkers. We will also measure the economic impact of such interventions in a cost-benefit analysis.

**Methods:**

We propose 3 ecologically valid intervention packages (cognitive stimulation, physical activity, or both combined) and aim to assess them against a control group. We will target a sample of 400 participants as representative of the population of community-dwelling aging citizens in Malaysia (aged 60 years and older). The 5 projects of this study examined (1) psychology (social interaction and emotional well-being); (2) neuroscience, looking at neural markers of cognition (magnetic resonance imaging and electroencephalogram); (3) decision-making (risk and challenges in decision making); (4) economics (cost-benefits and effectiveness of the study interventions); and (5) biological markers of aging, using salivary samples. The Sunway University Institutional Review Board has reviewed and approved the study (SUREC2020/039).

**Results:**

Briefly, primary outcomes will include changes in cognitive scores (Montreal Cognitive Assessment), changes in cognitive behavioral measurements, changes in electroencephalogram and structural magnetic resonance imaging, changes in everyday problem-solving and Iowa gambling task scores, changes in salivary biomarkers (lactoferrin, C-reactive protein, and telomere length), and cost-benefit analysis of the intervention. The study grant was awarded in August 2019, with recruitment starting in May 2022 and concluding in July 2023. In 2023, the intervention phase began and is currently ongoing, with the first publications of outcomes expected in 2026.

**Conclusions:**

The effectiveness of these interventions will be examined from the perspective of multiple disciplines, including psychology, neuroscience, biology, and economics. We anticipate that the results of our study will be of interest to both the academic and general community and will hopefully influence policymaking. We hope that this study will provide robust and impactful, evidence-based insights on healthy aging and, thus, contribute to improving the overall quality of life associated with aging.

**Trial Registration:**

ClinicalTrials.gov NCT06376656; https://clinicaltrials.gov/study/NCT06376656

**International Registered Report Identifier (IRRID):**

DERR1-10.2196/88268

## Introduction

### Background

There is a consensus from both cross-sectional and longitudinal research on the pattern of changes associated with aging, especially among older adults. With aging comes a natural decline in muscle mass and strength, leading to risks such as falls, fractures, disability, and a loss of independence [1]. Along with physical decline, research evidence has shown nearly a linear decline in cognitive function based on measures representing efficiency or effectiveness of information processing [2]. Research conducted in the United Kingdom and Malaysia has shown much poorer performance in theory of mind and working memory in the Malaysian older adult population compared to the other 3 groups (British young and older adults and Malaysian young adults). Many of these findings are moderated by educational levels, which suggests that interventions aimed at older adults need to be targeted accordingly [3]. According to Carstensen [4,5], the sense of future time, particularly the approach of endings such as the end of life, elicits cognitive, emotional, and motivational changes [4,5]; for example, aging is associated with a trend toward favoring positive over negative stimuli in cognitive processing [6]. This potentially introduces risks regarding how older adults make important decisions that have financial consequences in their daily lives; this is supported by evidence from research linking age-related changes in brain activity and physiology with financial decision-making [7,8].

At present, there is promising evidence that cognitive training and physical activity may delay the decline of and possibly increase gray matter volume in the brain [9,10]. There is evidence suggesting that physical activity plays a critical role in preserving muscle mass, maintaining mobility [11], and enhancing neuroplasticity [12], whereas cognitive stimulation through activities that challenge attention, memory, and language supports mental agility and resilience [13]. Importantly, both physical and cognitive domains are closely linked to the performance of basic and instrumental activities of daily living, underscoring the need for interventions that integrate these components. However, these studies are often conducted in laboratories using traditional cognitive and memory tasks with little ecological validity and minimal consideration of general everyday life. Furthermore, most studies are conducted in the Western world; it is unclear whether such interventions are suitable for non-Western populations such as Asian individuals. In addition, most training interventions are conducted in brief timescales, and it is not clear whether these effects remain stable in the long term [14]. On the basis of systematic reviews by Masini et al [15] and Bibi et al [16], most interventions in older adults, including physical activity, cognitive training, or behavioral interventions, are conducted across durations ranging from 12 weeks to 12 months, with outcome assessments limited to immediately after the intervention or short follow-up periods (within 6 months). While there is a lack of universal agreement on the duration of long-term interventions, the long-term effects of physical activity are defined as at least 24 months of intervention and follow-up to better determine the effectiveness of measured physical activity [17]. Studies examining interventions using physical activity and cognitive training to promote healthy aging in older adult populations have mostly been conducted among Western populations [18-20], implying a potential research gap in studying the effectiveness of these interventions in older adults from non-Western populations (eg, Asian individuals) and exploring the cultural and socioeconomic determinants that may influence these populations’ participation and engagement [16,21,22]. Our own systematic review showed that physical activity interventions work best in combination with simultaneous cognitive stimulation interventions in terms of improving cognitive outcomes in older adults and that a longer duration matters (more than 20 sessions) [23]. Moreover, conducting interventions in communities improves ecological validity, particularly by placing age-related decline within the relevant sociocultural context, and has potentially a large social and economic impact in those communities. However, a major challenge for long-term interventions is engagement and acceptability, which depend largely on motivational factors. To increase participants’ engagement, socioculturally relevant motivational needs need to be considered, and cost-benefit analyses need to be included to understand the mechanisms of long-term voluntary engagement in such interventions.

In addition, the use of salivary biomarkers for aging is of interest due to their noninvasive nature and cost-effectiveness, along with the advancement of various analytical assays. Current research efforts focused on the identification of salivary biomarkers in the diagnosis and monitoring of disease progression may be useful to predict cognitive decline. Crucially, using these biomarkers to monitor intervention efficacy addresses a significant gap in the literature, as they are rarely applied as dynamic measures of progress. These biomarkers include lactoferrin, a potential predictor of early development of dementia and Alzheimer disease [24]; C-reactive protein (CRP), as elevations in its systemic concentrations are also associated with the risk of developing metabolic-related and neurodegenerative diseases [25,26]; and telomere length, a suggested candidate biomarker to indicate individual variability in aging and risk of specific health conditions in older adults [27,28].

The overarching aims of this project are to assess cognitive function across a broad range of measures, contextualize these measures within additional demographic and lifestyle data, implement and validate evidence-based interventions derived from theories of cognitive decline that incorporate both physical and cognitive activities, and assess the effectiveness of these interventions in modulating the trajectory of age-related cognitive decline in a socioeconomically and ethnically diverse Asian sample. The main objectives and specific objectives are summarized in the following sections. In this paper, we propose the comparison of 3 long-term interventions (cognitive stimulation, physical activity, and combined cognitive stimulation and physical activity) against a passive control condition. These interventions will be administered over an extended period (4 years). We hypothesize that these interventions can, over 4 years, significantly slow down the normal rate of aging-related decline in cognitive function and brain structure and function, and change the expression of aging-related salivary biomarkers. We predict that cognitive stimulation and physical activity will lead to a significant reduction in aging-related decline as compared to the nonintervention control. In addition, we predict that the combined cognitive stimulation and physical activity intervention will yield the most significant reduction in aging-related decline as compared to cognitive stimulation alone, physical activity alone, and the control condition. The overall structure of the program is shown in Figure 1. These 5 separate projects are interrelated not only because they involve the same participants but, more importantly, because they all aim to delay aging-related decline. Age-related decline is manifested in individuals’ cognitive and behavioral functions, neural markers of cognition, decision-making, and biological markers. The effectiveness of the cognitive and/or physical interventions will be measured (projects 1, 2, 3, and 5), and the economic impact of such long-term interventions in a cost-benefit analysis will also be evaluated (project 4).

**Figure 1 figure1:**
[figure not shown]
Overview of the study. EEG: electroencephalogram; MRI: magnetic resonance imaging.

### Main Objectives

The main objectives of this study are to (1) examine whether these interventions can, over 4 years, significantly slow down the normal rate of aging-related decline in cognitive function, physical performance, and brain activity and measure the economic impact of such interventions; (2) test hypotheses derived from aging-related theories; (3) provide robust, measurable evidence in both the short and long term and validate meaningful interventions (positive results or improvements in cognition, mental, and physical health that we are going to implement as being acceptable and sustainable in the long term); and (4) provide a quantifiable cost-benefit ratio for suggested solutions.

### Specific Objectives

There are 5 projects in this study. Briefly, we will examine older adults’ self-report and behavioral (task-based) markers of cognitive function (project 1), structural and functional brain measures (project 2), decisions impacting important and less important aspects of daily life (project 3), and cost-benefit analyses and economic gains and losses of the interventions (project 4), as well as identifying the effects of the interventions on aging-related salivary biomarkers (project 5). The specific objectives by project are summarized in Multimedia Appendix 1.

## Methods

### Trial Design

This quasi-randomized controlled trial has a longitudinal mixed-subject design for a total of 4 years (between-subject: intervention type; within-subject: repeated measures on various tasks and assessments). Participants will be quasi-randomly allocated to 1 of the 4 groups (cognitive stimulation, physical activity, combined cognitive stimulation and physical activity, and control) in a sequential cycle by experimenters to ensure balance in group sizes. Minor adjustments may be made for a small proportion of participants (anticipated to be fewer than 15% of the intervention sample) to accommodate logistical feasibility, such as availability during intervention sessions or access to required resources (eg, internet-enabled devices for online cognitive sessions). These adjustments will be applied only when necessary. Participants and experimenters will not be blinded to group assignment. Participants will be tested at baseline and every 6 months until the end of 4 years. Structural magnetic resonance imaging (MRI) will only be performed at baseline and at the end of the intervention period.

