### Recruitment

Recruitment of participants will be conducted by advertising on social media, as well as visiting community clubs and meeting with community leaders in different housing areas across different socioeconomic strata. We refer to this cohort as the MyAgeWell cohort.

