## Results

From the perspective of psychology, primary outcomes will be the changes in cognitive scores (MoCA), cognitive behavioral measurements, everyday problem-solving, and Iowa gambling tasks. From the perspective of neuroscience, primary outcomes will be the changes in EEG and MRI. From the perspective of economics, the primary outcome will be the cost-benefit analysis of the intervention. From the perspective of biology, primary outcomes will be the changes in salivary biomarkers (lactoferrin, CRP, and telomere length).

The study grant was awarded in August 2019. Participant recruitment was delayed due to the COVID-19 pandemic, as the target population comprised healthy older adults who were particularly vulnerable during periods of movement restrictions and heightened infection risk. Recruitment commenced in May 2022 and was completed in July 2023. A total of 400 healthy older adults were successfully enrolled. The intervention phase began in 2023 and is currently ongoing, with participants undergoing intervention activities and follow-up assessments at 6-month intervals throughout the study period. At the time of manuscript submission, follow-up data collection and data analysis are ongoing. Baseline characteristics and cross-sectional findings from the cohort have been reported separately, while analyses of intervention-related outcomes are currently underway. The first intervention outcome publications are anticipated from 2026 onwards as follow-up assessments are completed, and additional longitudinal data are available for analysis.

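### Arms are assigned in a non-random cycle by unblinded experimenters who may override it, and neither the limitations nor the analysis carries the resulting risk of selection bias

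*Protocol article*

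**What the plan says.** All of the following is in the protocol article.

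- **Trial Design** gives the label: "This quasi-randomized controlled trial has a longitudinal mixed-subject design for a total of 4 years". It then gives the method: "Participants will be quasi-randomly allocated to 1 of the 4 groups", "in a sequential cycle by experimenters to ensure balance in group sizes". Equal group size is the only reason stated.
- The same section allows departures: "Minor adjustments may be made for a small proportion of participants (anticipated to be fewer than 15% of the intervention sample". The examples given are "availability during intervention sessions or access to required resources (eg, internet-enabled devices for online cognitive sessions".
- It also states: "Participants and experimenters will not be blinded to group assignment".
- **Statistical Methods** compares the four arms on baseline and post-intervention values in a mixed model. It names age and sex as example covariates and declares significance at P below .05.
- **Expected Findings** and **Strengths and Limitations** discuss the unequal contact time of the combined arm and the urban sample. Neither mentions allocation.
- **Results** reports: "A total of 400 healthy older adults were successfully enrolled". Recruitment ran from May 2022 to July 2023, and the intervention phase began in 2023.

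The article does not give the order or starting point of the cycle. It also does not say whether a person's arm was set before or after consent, eligibility checks and baseline testing.

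**The concern.** A sequential cycle has no chance element. Anyone who knows the order and the last assignment knows which arm is due next, and here the people applying the cycle know the arms. There are three ways in which selection could enter:

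1. **Who is enrolled**, if the arm due was known at entry.
2. **The order in which people are placed in the cycle**, which matters even if allocation followed enrolment.
3. **The overrides**, which depend on availability and device access. These are characteristics of the participant and may go with health, education or income.

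The between-arm P values treat the arms as exchangeable at the start. If they differ in motivation, health or support, and those factors affect the four-year rate of decline, the difference appears as an intervention effect. Every contrast with control, and every contrast between active arms, is exposed. The trial hopes to inform policy, so readers need to know how much of an observed effect could come from allocation.

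**Working it through.** **Reproducing the plan's own figures**

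Inputs from Sample Size: 80 per group, partial eta squared 0.06, power 86.6%, 20% attrition. Input from Statistical Methods: alpha .05, taken as two-sided.

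- Total: 4 × 80 = 320, and 320 / (1 − 0.20) = 400. This matches.
- Power of the 2 × 2 interaction: f² = 0.06/0.94 = 0.0638. With λ = f² × 158 = 10.09 on F(1, 158), power is 88.4%, within 2 points of the stated 86.6%.
- The standardised difference in change that gives exactly 86.6% with 80 per arm is d = 0.488. Check: λ = 0.488² × 80/2 = 9.53, and 9.53/(9.53 + 158) = 0.057, which rounds to 0.06.

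The sample size is therefore not in dispute.

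**How predictable the next assignment is**

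| Scheme, four arms | Next arm guessed correctly |
|---|---|
| Cycle followed without exception, order known | 100% (upper bound) |
| Cycle with 15% of the 300 in active arms overridden (45 people) | 1 − 45/400 = about 89% |
| Cycle with 15% of all 400 overridden (60 people) | 1 − 60/400 = 85% |
| Random permuted blocks of 4, past assignments visible (simulation) | about 52% |
| Random blocks of 4, 8 or 12, past assignments visible (simulation) | about 46% |
| Simple randomisation | 25% |

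The override rows use the full 15% allowance. The article anticipates fewer.

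**What an assumed bias would do**

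The documents give no figure for the bias, so this is an illustration. Suppose selection shifts the expected change in an active arm relative to control by b SD of change, with no true effect. For a two-sample t test on change with 80 per arm, the noncentrality is b × √(80/2) = 6.32b, with 158 degrees of freedom and critical value 1.975.

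| Assumed b (SD of change) | Noncentrality | False-positive rate |
|---|---|---|
| 0 | 0 | 5.0% |
| 0.05 | 0.32 | 6.1% |
| 0.10 | 0.63 | 9.6% |
| 0.15 | 0.95 | 15.6% |
| 0.20 | 1.26 | 24.2% |

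A shift of 0.10 is about one fifth of the effect behind the stated power (0.10/0.488 = 0.20).

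**How close the tipping point would be**

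The standard error of the difference is √(2/80) = 0.158 SD of change, so the smallest significant difference is 1.975 × 0.158 = 0.312. If a trial of this size observed 0.488, a bias of 0.488 − 0.312 = 0.176 SD of change would be enough to remove significance.

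**What the planned covariates can do**

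Age and sex do not capture motivation, health, education or device access. In a model where baseline and follow-up are both responses, a covariate entered only as a main effect shifts the level at both times. With complete data it leaves the estimated difference in change untouched. Adjusting the change requires covariate-by-time terms.

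**The case against.** The strongest reply is that the trial is candid. It calls itself quasi-randomized, describes the cycle, gives its reason, and discloses the overrides and the lack of blinding. That stands: a reader might infer that the trial presents itself as fully randomised, and the text does not support this. The fair criticism is that the disclosed weakness goes no further than the design section.

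Two other stronger readings also fail:

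- **That every assignment was known before a person was enrolled.** The order of the cycle and the timing of allocation are not stated, and some people may depart from the cycle. The recruitment and intervention dates are compatible with allocation after enrolment. Steering at entry would then be limited, and the risk would move to placement in the cycle and to the overrides. The 100% figure is an upper bound.
- **That recruiters steered particular people.** The article says recruitment included "visiting community clubs and meeting with community leaders in different housing areas across different socioeconomic strata". It does not say that recruiters also allocated, that people entered in groups, or that arms lined up with booking slots.

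It is also right that the size of b has no basis in the documents, and that a stable difference in level would largely cancel in a baseline-to-follow-up comparison. Only selection related to the rate of change does harm. A condensed article may leave out concealment procedures, so their absence cannot be asserted. None of this removes the point, because the cycle, the unblinded staff and the discretionary overrides are stated rules and not missing detail.

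**Conclusion.** The concern holds in this form: allocation is cyclic and non-random, is applied by unblinded staff with discretion to override, and is largely predictable to those who know the order. The limitations and the primary analysis do not reflect this.

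The size of any bias cannot be derived from the documents, and nothing shows that selection took place. On the stated assumptions (80 per arm, two-sided .05, no true effect, and a shift of 0.10 to 0.20 SD in expected change), the false-positive rate per contrast would be about 10% to 24% instead of 5%. The point affects what the trial may conclude about cause. It does not affect its sample size or nominal power.

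**What to change.** All 400 people are enrolled and the intervention has begun, so the allocation section should not be rewritten as though another method had been used. Before outcomes are interpreted:

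1. **Describe and limit.** Call the allocation non-random, cyclic and unconcealed (unless concealment is documented). Say in the limitations and conclusions that selection bias cannot be excluded.
2. **Report what happened.** State when and by whom allocation was made. From whatever records exist, tabulate arm due against arm given, with the reason for each override. Add a sensitivity analysis by arm due in the cycle. This deals with the overrides but not with the order in which people were placed.
3. **Adjust.** Pre-specify prognostic factors already collected at baseline in addition to age and sex, for example education, health and physical activity status, and socioeconomic status. Enter them with time interactions so that they act on change.
4. **Tipping point.** For each claimed effect, give the between-arm difference in expected change, in SD of change, that would remove it.

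If any assignment is still to be made, use a concealed list in random permuted blocks, which also keeps group sizes balanced.

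The cost is some protocol and analysis-plan text, one table if the records allow it, and two or three extra analyses. No new participants or staff are needed. The downside is a more cautious causal claim.
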